### Sample size calculation and statistical analysis

2.9

We hypothesise that all treatment groups lead to a statistically significant reduction in symptoms of depression between baseline and week 8 (within group effect). We also hypothesize that the groups do not differ in terms of treatment success (between group effect). We performed a power analysis to calculate the sample size. With a sample size of N = 105 patients, an alpha error probability of 0.5 and a moderate effect size (0.5) (for change in symptoms of depression), we achieve a statistical power of >0.8. An effect size of 0.5 equates to a mean difference in the MADRS score between baseline and week 8 of 50%, which reflects a commonly accepted clinical response measure in depression studies. In practise , this would mean a reduction of 15 points on the MADRS scale from 30 points at baseline to 15 points at week 8. Such a kind of reduction has been seen in other interventional studies in depression.

Data analysis will be conducted by the team at the Department of Psychiatry, University of Münster. The primary and secondary outcome measures will be analysed using an intention-to-treat (ITT) and exploratory approach. We will focus on specialized analyzation for longitudinal data. In addition, we will correct for confounding variables in all analyses where significant differences arise between the groups.

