The choice of statistical test will depend on the nature of the data and the specific research question. For continuous outcome variables (e.g., scores on depression rating scales, quality of life scores, continuous physiological measures), Analysis of Variance (ANOVA) or independent samples t-tests will be used to compare means between the three treatment groups (Ayurvedic-only, Allopathic-only, and Combination). *Post-hoc* tests (e.g., Tukey’s HSD, Bonferroni correction) will be employed if significant differences are found between groups to determine which specific groups differ significantly. For categorical outcome variables (e.g., presence or absence of adverse events, categorical measures of quality of life, treatment adherence categories), Chi-square tests or Fisher’s exact tests (for small sample sizes) will be used to compare proportions between treatment groups. Given the repeated measures design (baseline, 8 weeks, 3 months, 6 months), appropriate statistical models for longitudinal data (e.g., repeated measures ANOVA, mixed-effects models) will be used to analyse changes in outcome measures over time within each treatment group and to examine the interaction effects between treatment group and time. This will allow for a more powerful examination of treatment effects and the assessment of treatment response trajectories. Strategies to address missing data will be carefully considered and documented. In addition to p-values, effect sizes (e.g., Cohen’s d) and 95% confidence intervals will be reported for all significant findings. All statistical analyses will be performed using appropriate statistical software packages (e.g., SPSS, R).

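### The power statement prints an alpha of 0.5 and does not identify the test behind its power above 0.8; at alpha 0.05 and d = 0.5 that figure covers the within-group change in one arm or pooled, but not joint success in three arms or a between-arm contrast

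*Protocol article*

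**What the plan says.** Section 2.9 (Sample size calculation and statistical analysis) states two hypotheses. The first is within-group: "We hypothesise that all treatment groups lead to a statistically significant reduction in symptoms of depression between baseline and week 8". The second is between-group: "We also hypothesize that the groups do not differ in terms of treatment success (between group effect").

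One power statement follows: "With a sample size of N = 105 patients, an alpha error probability of 0.5 and a moderate effect size (0.5"). The effect is described as "a moderate effect size (0.5) (for change in symptoms of depression"), and the result is "we achieve a statistical power of >0.8". It names no test and no sidedness. It does not say whether the n behind the figure is 105 or 35, or whether 0.5 is Cohen's d, a paired standardised change or Cohen's f.

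The section then translates effect size 0.5 into a halving of the MADRS score, that is, "a reduction of 15 points on the MADRS scale from 30 points at baseline to 15 points at week 8".

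Later in the same section, between-group comparisons are planned by ANOVA or t-tests and change over time by repeated-measures or mixed models. The reporting rule is that "effect sizes (e.g., Cohen’s d) and 95% confidence intervals will be reported for all significant findings".

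Section 2.1 gives about 35 patients per group. Section 1.2 starts from the assumption that allopathic and Ayurvedic treatment are equally effective and expects no significant between-group difference at week 8.

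**The concern.** There are three problems in one short statement.

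- **Alpha.** A type I error of 0.5 means that half of all tests with no true effect would be called significant. It does not fit 95% intervals, which correspond to a two-sided 0.05.
- **Unlabelled figure.** The power claim comes directly after a within-group and a between-group hypothesis, and nothing says which one it serves.
- **Effect size.** A standardised effect and a percentage reduction are different quantities. Equating them leaves the assumed SD undefined.

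The between-group result is the main thing at stake. The authors expect a non-significant difference. If that result is read beside a stated power above 0.8, it can be taken as evidence that the treatments work equally well, although arms of 35 would often miss a half-SD difference.

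**Working it through.** **Inputs from section 2.9 and section 2.1.** N = 105; 35 per arm; alpha 0.5 as printed; effect size 0.5; MADRS 30 to 15.

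**Assumptions of this check.** The tests are two-sided. The corrected alpha is 0.05, matching the 95% intervals. The effect size is read as a standardised mean difference (d) unless stated otherwise. A paired t-test stands in for the unnamed within-group test.

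**Formulas.** Paired test: noncentral t with n − 1 df and noncentrality d·√n. Two arms: noncentral t with 2n − 2 df and noncentrality d·√(n/2). Joint power in three arms: (single-arm power)³, treating the arms as independent.

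**1. The plan's figure as printed (alpha 0.5, d = 0.5)**

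| Test | Power |
|---|---|
| Paired, one arm of 35 | 0.989 |
| All three arms | 0.989³ ≈ 0.966 |
| Two arms, 35 vs 35 | 0.924 |
| Three-group ANOVA, f = 0.25 | 0.953 |

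The claim of more than 0.8 is reproduced, but every test in the table satisfies it, so it does not discriminate between them.

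**2. Alpha 0.05, d = 0.5, within-group**

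- One arm of 35: noncentrality 0.5 × √35 = 2.958, critical t 2.032, power 0.820.
- One arm with fewer completers: 34 gives 0.808, 33 gives 0.795, 30 gives 0.754.
- Pooled over 105: noncentrality 0.5 × √105 = 5.123, power 0.999.
- All three arms significant: 0.8195³ = 0.550; with 30 completers per arm, 0.754³ = 0.429.

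The single-arm test needs 34 patients for 0.80, close to the 35 per arm that make up 105. It is therefore a plausible origin of the figure, with 0.5 a misprint for 0.05. That is an inference.

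**3. Alpha 0.05, d = 0.5, between-group at one time point**

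- 35 vs 35: noncentrality 0.5 × √17.5 = 2.092, critical t 1.995, power 0.541.
- With Bonferroni for three pairs (0.05/3): 0.365.
- Three-group ANOVA, N = 105, f = 0.25: 0.612.
- Power 0.80 for 35 vs 35 is reached only at d of about 0.68.

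**4. The 15-point translation**

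If 15 points is a standardised change of 0.5, the SD of change is 15 / 0.5 = 30 points, as large as the assumed baseline mean. The article gives no SD, so the table shows a range of assumed values (paired test, n = 35, alpha 0.05).

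| Assumed SD of change | d = 15/SD | One arm | All three arms |
|---|---|---|---|
| 10 | 1.50 | >0.999 | >0.999 |
| 15 | 1.00 | >0.999 | >0.999 |
| 20 | 0.75 | 0.991 | 0.972 |
| 25 | 0.60 | 0.932 | 0.81 |
| 30 | 0.50 | 0.820 | 0.550 |

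The within-group conclusion therefore depends on which half of the section's own equation is meant.

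**The case against.** A reader might infer that the claimed power holds for a single-arm test only and is wrong for both hypotheses. The documents do not support that, for four reasons.

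- **Other readings pass at alpha 0.05.** The pooled pre-post test, which uses the N that the article quotes, has 0.999. One-way ANOVA has 0.997 if 0.5 means Cohen's f. A two-time-point group-by-time interaction with f = 0.25 and an assumed correlation of 0.5 also gives 0.997. The longitudinal models planned in section 2.9 use all 105 patients, so not every planned test rests on 35. This stands. However, the first hypothesis is stated for all groups, which a pooled test does not address. An f of 0.5 is conventionally large, whereas the article says moderate. The interaction reading has noncentrality 105 × 2 × 0.25² / (1 − 0.5) = 26.25 = 105 × 0.5², so it is the same large f of 0.5 applied to change scores.
- **The joint shortfall depends on d = 0.5.** Under the article's own 15-point target, joint power in three arms falls below about 0.8 only if the SD of change exceeds about 25. It is also tempting to say that the plan leaves no room for dropout. That too requires d = 0.5: at an assumed SD of 15, joint power with 28 completers per arm is still 0.997. Both objections stand.
- **The article does not expressly claim power for the between-group comparison.** It ties the effect size to symptom change from baseline to week 8. That hypothesis is one of no difference, so power to detect 0.5 SD is not its power; a margin would be needed, and none is given. This stands. The fault is that the figure is unlabelled after both hypotheses.
- **The study calls itself exploratory, and its conclusions call the data hypothesis-generating.** This tempers the consequences. It does not excuse a wrong alpha in a power analysis presented as the basis of the sample size.

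**Conclusion.** The point holds in limited form.

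- **Certain from the text:** alpha is printed as 0.5, conflicts with the 95% intervals, and makes the power figure uninformative (0.92 even for 35 vs 35 at d = 0.5). This is the part that must be corrected.
- **Certain from the text:** the figure has no named test, n or effect metric, and the 50% translation implies an SD of change of 30 points.
- **Conditional on two-sided alpha 0.05 and d = 0.5:** the figure is right for one arm of 35 (0.82; 0.75 with 30 completers) and for the pooled change (0.999). It does not hold for significance in all three arms (about 0.55, independent arms) or for a contrast between two arms of 35 at week 8 (0.54).
- **Sensitivity:** the joint-arm shortfall disappears if the 15-point change is the real target and its SD is 20 or less. The between-arm shortfall for a 0.5 SD difference at one time point does not depend on that choice.

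The sample size itself is not shown to be wrong.

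**What to change.** Amend section 2.9 and keep N = 105:

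1. Correct alpha to 0.05, two-sided.
2. Name the test, the n (35 per arm or 105 pooled) and the effect metric behind the power figure.
3. Drop the sentence that equates effect size 0.5 with a 50% reduction, or state the assumed SD of MADRS change and recompute. For a 15-point change, joint three-arm power is above 0.97 for an SD of 20 or less, and 0.81 at 25.
4. State that the power above 0.8 refers to the within-group change. Add that a between-arm contrast of 0.5 SD has about 0.54 power (0.80 only at about 0.68 SD), so a non-significant between-group result does not show equal effectiveness.

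The cost is wording and, if an SD is chosen, one recalculation; no extra patients are needed. The downside is that the stated power becomes less favourable for the comparison that readers care about most.

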### Trial design and study setting

2.1

This study employs a naturalistic observational (non-randomization) design, conducted within real-world clinical settings for a six-month period (see **Figure 1**) where the group assignment reflects patient preference and clinical practice in specialized hospitals. The study population comprises 105 adult participants. Participants will be observed in one of three treatment groups, each consisting of approximately 35 individuals, based on the treatment they receive (see **Figure 1**).

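### The sample-size text equates a standardised effect of 0.5 with a 50% (15-point) MADRS fall, which is true only if the SD is 30 points

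*Protocol article*

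**What the plan says.** The sample-size paragraph of the protocol article (section 2.9) gives four inputs or results: "With a sample size of N = 105 patients", "an alpha error probability of 0.5", "a moderate effect size (0.5) (for change in symptoms of depression") and "we achieve a statistical power of >0.8". Section 2.1 describes three groups, "each consisting of approximately 35 individuals".

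The paragraph then puts the effect size into clinical terms. It says "An effect size of 0.5 equates to a mean difference in the MADRS score between baseline and week 8 of 50" per cent, adds that this is a quantity "which reflects a commonly accepted clinical response measure in depression studies", and gives a worked example: "this would mean a reduction of 15 points on the MADRS scale from 30 points at baseline to 15 points at week 8". It closes by saying that reductions of this kind have been seen in other interventional studies.

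No SD of MADRS, SD of MADRS change or correlation between baseline and week 8 is given. Later in section 2.9, Cohen's d is named as the example of an effect-size measure for reporting.

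**The concern.** The figures 0.5 and 50% look alike but have different denominators. The effect size that enters a power calculation for a mean change is that change divided by an SD. The 50% in the text is the change divided by the baseline mean. One can be turned into the other only through an SD, and the paragraph has none.

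What is at stake is the meaning of the sample size. The sentence is the only clinical justification offered for N = 105, and it concerns the primary endpoint. A reader is told that the study is sized for a halving of the MADRS score. The calculation behind the power figure concerns half an SD, which on ordinary assumptions is a much smaller fall. The appeal to reductions seen elsewhere then supports 15 points, not the effect actually used, and nothing in the text justifies that smaller effect.

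**Working it through.** **Inputs from the protocol article.** N = 105 and effect size 0.5 on change in symptoms (section 2.9); about 35 per group (section 2.1); power above 0.8; stated translation 50%, or 15 points from a baseline of 30 (section 2.9).

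**Assumptions.** Alpha is printed as 0.5; I take 0.05, two-sided. The SD of change is not stated; I show 8, 10, 12 and 15 points.

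**Step 1: reproduce the stated power.** The text ties the effect to the change from baseline to week 8, so the natural test is a paired t-test within one group.

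- Noncentrality = d × √n = 0.5 × √35 = 2.96, with 34 degrees of freedom.
- Power at two-sided alpha 0.05 = 0.82.
- Number needed for 80% power = 33.4, so 34 per group; 3 × 35 = 105.

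This agrees with the stated figure and with the group size. Other set-ups also exceed 0.8: all 105 patients in one paired test (0.999), a three-group ANOVA with f = 0.5 (0.997), or the paired test with n = 35 and alpha as printed (0.989). In each of them 0.5 is a standardised quantity. None of them takes a percentage change as input.

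**Step 2: test the stated equation.** With d = mean change / SD, the SD that makes 15 points equal to d = 0.5 is

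SD = 15 / 0.5 = 30 points.

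This equals the illustrative baseline mean and is twice the mean change. If changes were roughly normal with mean fall 15 and SD 30, the share of patients getting worse would be Φ(−15/30) = Φ(−0.5) = 31%. Another 31% would fall by more than 30 points. That is not a believable picture of the trial that the paragraph describes. Standardising by the SD of the scores instead of the SD of change does not help, because that SD would also have to be 30.

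**Step 3: translate correctly over a range of SDs.** Points at d = 0.5 are 0.5 × SD; the effect size for 15 points is 15 / SD; the overstatement is 15 / (0.5 × SD).

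| Assumed SD of change | Points at d = 0.5 | As % of 30 | Overstatement | d for 15 points | n per group for 80% power at 15 points |
|---|---|---|---|---|---|
| 8 | 4 | 13% | 3.75 | 1.88 | 5 |
| 10 | 5 | 17% | 3.0 | 1.50 | 6 |
| 12 | 6 | 20% | 2.5 | 1.25 | 8 |
| 15 | 7.5 | 25% | 2.0 | 1.00 | 10 |
| 30 | 15 | 50% | 1.0 | 0.50 | 34 |

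The last row shows the only SD at which the article's equation holds.

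**Step 4: effect on power.** If a 15-point fall is really expected, a paired test with 35 patients has power of at least 0.999 for SDs of 10 to 15. The mistake therefore does not weaken the within-group test.

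**The case against.** The best case on the other side is that nothing operational depends on the sentence. The stated power reproduces, and N, endpoint, time point and contrast are the same under either reading. The error is on the safe side: a study sized for half an SD will detect a 15-point fall almost surely. The article also calls itself exploratory and hypothesis-generating. All of this stands, and it limits the point to a wrong explanation of a usable calculation. It does not make the equation true, and no other part of the article repairs it.

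Five stronger readings are tempting, and the document does not support them.

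- *A fixed factor, such as threefold.* That is exact only at an assumed SD of 10. With no SD in the article, only a range can be given.
- *An SD of 30 is impossible because nobody can fall by more than 30 points.* The 30 is an illustrative mean, not every patient's score; a patient who starts higher can fall further. The SD is implausible, not ruled out by that argument.
- *The study is underpowered because of this error.* Within-group power is not reduced.
- *The error undermines the comparison between arms.* The 0.5 is tied to change from baseline to week 8, and the text does not say that the between-group contrast was the one powered. Power for that contrast, and the printed alpha of 0.5, are separate matters.
- *The article misdefines response.* It says only that a 50% fall reflects an accepted response measure. A response criterion applied to each patient is indeed different from a halved group mean, but the article sets no responder definition that it then contradicts.

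**Conclusion.** The equation of 0.5 with a 50%, 15-point fall is wrong as written. It holds only for an SD of 30 points. For an assumed SD of change between 8 and 15 points, the calculation is sized for a mean fall of 4 to 7.5 points, so the 15 points in the text overstates it by about 2 to 4 times. Put the other way, 15 points would be an effect size of about 1.9 to 1.0.

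The multiple rests entirely on the assumed SD, because the article states none. Reading 0.5 as standardised rests on its label as moderate, on the naming of Cohen's d, and on the stated power reproducing at 0.82 under an assumed two-sided alpha of 0.05. The consequence is confined to the clinical justification of the sample size. Neither the within-group power nor the number of patients is called into question by this error.

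**What to change.** Delete the sentence that equates 0.5 with 50%, together with the 30-to-15 example as an explanation of it. Then do one of two things.

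1. Keep d = 0.5. State that it is the mean change divided by the SD of change for the within-group contrast from baseline to week 8; give the assumed SD and its source; and give the matching MADRS points, for example 5 points if the SD is 10. Justify that number of points, and drop or replace the remark about reductions seen in other studies, which concerns 15 points.
2. Keep 15 points as the target. Restate the calculation with d = 15 / SD and the assumed SD. For SDs of 8 to 15 this needs only about 5 to 10 patients per group, so the text should then say what else motivates 35 per group.

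Either option costs a few sentences and no change in N. An analysis of patients with at least a 50% fall could be added if it is of interest, but it is optional and not needed to correct the error.

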**Methods:**

This six-month, naturalistic observational study will involve 105 adult participants (18–65 years) diagnosed with MDD according to DSM-5 criteria. Participants will be categorized to one of three groups: allopathic-only treatment (n=35), ayurvedic-only treatment (n=35), or a combination of both (n=35). Depressive symptom severity will be assessed as primary endpoint using primarily the MDRS, and secondarily HAMD and PHQ-9 scales at baseline, every 2 weeks until week 8, followed by monthly assessments until months 6. Secondary outcomes will exploratively include side effects (UKU, GASE, MARS), quality of life and daily functioning (WHOQoL-BREF, GAF, FAST) as well as general health measures (e.g. lab tests).

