Ayurvedic medicine, an ancient holistic system originating from India, offers an alternative and complementary approach to MDD (10). This system emphasizes the interconnectedness of mind, body, and spirit, aiming to restore balance through various interventions. These include herbal remedies (e.g., Ashwagandha, Brahmi etc.), dietary modifications tailored to individual constitution (Prakriti), lifestyle adjustments promoting holistic well-being, and mind-body techniques such as yoga and meditation (11). Ayurvedic treatment is well established in India. It is a holistic whole system approach that traditionally consists of specific components (Panchakarma, manual therapies Dietary Modifications, Herbal Formulations, Lifestyle Modifications, Sattvavajaya and Daiva-vyapasraya-cikitsa) that are integrated into a common treatment approach. There are special hospitals that specialize in such holistic treatment concepts. Patients can choose whether they want to be treated in an allopathic or an Ayurvedic hospital. While level A (e.g. meta-analysis and RCTs) and level B (evidence from at least one high-quality study or multiple moderate-quality studies) evidence studies and some smaller studies suggest the potential efficacy of Ayurvedic treatments in alleviating depressive symptoms (12–14), robust, large-scale randomized controlled trials comparing Ayurvedic treatment to allopathic treatments are relatively scarce (15). Understanding the mechanisms through which Ayurvedic treatment exert their effects on mood and related symptoms remains an area of active research.

This necessitates a more comprehensive understanding of the relative treatment effects, side effects and potential synergistic effects of integrating allopathic and Ayurvedic treatments for MDD. A comparative evaluation of these approaches is crucial for informing evidence-based clinical practice and optimizing therapeutic strategies for individuals experiencing this pervasive and debilitating disorder. This study aims to address this critical gap in the literature through observation and analysis of real-world outcomes of allopathic and ayurvedic treatment modalities for MDD.

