### Study intervention

2.3

This study will utilize a naturalistic observational design, leveraging the established expertise and practices of two distinct clinical settings: Nadiad Ayurveda Hospital (for Ayurvedic only and combined treatments) and Shree Krishna Hospital, Department of Psychiatry, Bhaikaka University, Karamsad, Anand (for allopathic treatments). The assignment to the groups follows a clear system. The two hospitals have different areas of focus. One clinic (Shree Krishna Hospital) provides exclusively allopathic treatment, while the other (Nadiad Ayurveda Hospital) provides Ayurvedic treatment. Patients who are treated at the Ayurvedic hospital but have previously received allopathic treatment will continue to receive allopathic treatment (combined therapy). The clinic is selected based on clinical indications and in consultation with the patient.

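### Confounders are adjusted for only where groups differ significantly: at 35 per arm this gate lets moderate imbalances through, and it cannot correct for hospital in A vs B or A vs C

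*Protocol article*

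**What the plan says.** Section 2.9 of the protocol article (Sample size calculation and statistical analysis) gives one adjustment rule: "we will correct for confounding variables in all analyses where significant differences arise between the groups". It names neither the covariates nor the test level that triggers adjustment.

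Allocation is not random. Section 2.1 says that group membership reflects patient preference and clinical practice. Section 2.3 adds: "The clinic is selected based on clinical indications and in consultation with the patient". One hospital supplies all of Arm A and the Ayurveda hospital supplies Arms B and C. Within the Ayurveda hospital the split depends on treatment history: "Patients who are treated at the Ayurvedic hospital but have previously received allopathic treatment will continue to receive allopathic treatment (combined therapy").

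Two other sections bear on treatment history. Section 2.2.1 admits patients whatever treatment they have had earlier in the current episode. Section 2.3.3 also describes, under Arm C, patients in whom no allopathic treatment has been started.

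Sections 1.2 and 2.9 hypothesise that the groups do not differ. Section 3.2 acknowledges confounding and selection bias but offers no other adjustment method.

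**The concern.** With allocation by preference, indication and hospital, covariate adjustment is the main analytic protection for the between-arm comparison, which is the first objective in section 1.2. The rule makes that protection depend on a p-value in a small sample. A moderate imbalance in a strong prognostic factor can be non-significant and so go uncorrected.

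The sentence can also be read as adjusting only in analyses where the outcome differs significantly between groups. Confounding that hides a real difference would then never be corrected. Because the plan expects no difference, that failure would look like confirmation.

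A second problem is structural. Hospital differs between Arm A and the other two arms by design, so any test will flag it, yet no model can separate it from treatment in those contrasts.

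**Working it through.** **Inputs.** 35 patients per arm, 105 in total (abstract and section 2.1). The trigger level is not stated, so I assume two-sided 0.05. Section 2.9 prints "With a sample size of N = 105 patients, an alpha error probability of 0.5", which is a separate matter; I do not take 0.5 as the level of the screen. Covariate-outcome correlations of 0.3, 0.5 and 0.7 are assumed, because the document gives none. The outcome is whichever one is compared, week-8 score or change.

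**The plan's own figure.** Section 2.9 says "we achieve a statistical power of >0.8" for an effect size of 0.5. A paired within-arm t-test with n = 35, d = 0.5 and two-sided 0.05 has power 0.82, which agrees. With alpha at 0.5 as printed it is 0.989. Between arms at 0.05, power is 0.54 to 0.55 for a two-sample d of 0.5, and 0.61 for a three-group ANOVA with f = 0.25. The stated power therefore fits the within-arm test. A between-arm test, which is what the confounder screen is, does not reach it.

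**How often the screen flags a true imbalance.** For a pairwise t-test with 68 degrees of freedom, the noncentrality is d × √(35/2) = 4.18d.

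| True imbalance (SD) | Pairwise t-test | Three-group ANOVA |
|---|---|---|
| 0.2 | 13% | 10–12% |
| 0.3 | 24% | 18–23% |
| 0.4 | 38% | 30–38% |
| 0.5 | 54% | 44–56% |
| 0.8 | 91% | 85–94% |

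The ANOVA range depends on whether one arm stands apart or the three are evenly spread. Pairwise detection reaches 50% at 0.48 SD and 80% at 0.68 SD; for ANOVA the figures are 0.47–0.54 and 0.65–0.75. The smallest observed pairwise difference that can be significant is 1.995 × √(2/35) = 0.477 SD. For a binary factor, a 20-point difference is flagged 38–45% of the time and a 15-point difference 24–25%.

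**Bias left by the rule.** Simulation with 35 vs 35, one normal covariate, outcome = ρ × covariate + noise, no true treatment effect and 20,000 runs per case. With no adjustment the expected bias is imbalance × ρ, for example 0.3 × 0.5 = 0.15 SD.

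| Imbalance | ρ | Never adjust | Adjust if significant | Always adjust |
|---|---|---|---|---|
| 0.2 | 0.3 | 0.062 | 0.039 | 0.002 |
| 0.2 | 0.5 | 0.100 | 0.064 | 0.001 |
| 0.2 | 0.7 | 0.141 | 0.089 | 0.000 |
| 0.3 | 0.3 | 0.088 | 0.046 | −0.001 |
| 0.3 | 0.5 | 0.149 | 0.078 | −0.001 |
| 0.3 | 0.7 | 0.209 | 0.111 | 0.001 |
| 0.5 | 0.3 | 0.148 | 0.040 | −0.001 |
| 0.5 | 0.5 | 0.251 | 0.069 | 0.001 |
| 0.5 | 0.7 | 0.349 | 0.093 | −0.001 |

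Over these nine cases the type I error is 4.8–6.5% under the rule and 4.9–5.2% when always adjusting.

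**Hospital.** Take the columns intercept, B, C and hospital, where hospital = B + C. The rank is 3 with 4 columns, and the null vector is (0, 1, 1, −1). The A vs B contrast (0, 1, 0, 0) has product 1 with it, so it is not estimable; A vs C fails in the same way. The C vs B contrast (0, −1, 1, 0) has product 0, so it remains estimable. Fisher's test of hospital for A vs B gives p = 1.8 × 10⁻²⁰, so the screen is certain to flag a variable that it cannot correct for.

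**Prior allopathic treatment.** If every C patient and no B patient has it, as section 2.3 implies, it coincides with the C vs B contrast. If it varies within Arm A (illustrated with 17 of 35), arm plus prior treatment has rank 4 of 4. A coefficient can then be estimated, but only from Arm A patients, and applying it to C vs B is extrapolation.

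**The case against.** The case for leaving the text alone has weight. The study calls itself exploratory, section 3.2 names confounding and selection bias, and the hypothesis of improvement is within-arm, which the rule does not affect. A covariate list is commonly left to the analysis plan. For a single covariate the residual bias is about 0.1 SD at most, and the type I error hardly moves. All of this limits the severity. It does not remove the point, because section 2.9 states a rule rather than leaving one open, and the between-arm comparison is a listed objective.

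A reader might infer more than the document supports:

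- *That the rule leaves a bias of 0.15 to 0.25 SD.* That is the bias with no adjustment at all, for imbalances of 0.3 and 0.5 SD at a correlation of 0.5. The rule does adjust when it flags.
- *That it misses most important imbalances.* Pairwise, this holds only below about 0.48 SD. Imbalances above about 0.7 SD are mostly caught, and the document sets no threshold for an important one.
- *That no arm contrast can be estimated.* B vs C is within one hospital and is unaffected by hospital.
- *That prior allopathic treatment can never be adjusted for.* It can vary within Arm A (section 2.2.1) and perhaps within Arm C (section 2.3.3).
- *That Arm C had its antidepressant response before baseline.* The document gives no duration of, or response to, prior treatment.
- *That synergy is an aim to be dropped.* The phrase "relative treatment effects, side effects and potential synergistic effects of integrating allopathic and Ayurvedic treatments for MDD" is background rationale; none of the objectives in section 1.2 is synergy.

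**Conclusion.** The point holds in this form. The rule in section 2.9 is a poor way to select confounders in a non-randomised study with 35 per arm. It flags a 0.3 SD imbalance about one time in four and a 0.5 SD imbalance about half the time, and it leaves an average bias of about 0.04 to 0.11 SD per covariate that routine adjustment would remove. The harm is mainly bias, with type I error at most about 6.5%. Several confounders acting in the same direction could add up, but that was not simulated.

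These sizes rest on a two-sided 0.05 screen, correlations of 0.3 to 0.7, true imbalances of 0.2 to 0.5 SD and a linear covariate effect. The document gives no MADRS standard deviation; at an assumed SD of 10, the bias is 0.4 to 1.1 points.

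The hospital aliasing needs none of these assumptions. It follows from the allocation in section 2.3 and limits A vs B and A vs C under any covariate rule. For prior treatment, sections 2.3 and 2.3.3 do not agree on who is in Arm C, and they must be reconciled before the C vs B contrast can be described.

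**What to change.** In section 2.9, replace the significance condition with a prespecified covariate set that enters every between-arm model whatever the baseline tests show. Data that the study already collects or knows are enough: baseline MADRS, age, sex, in- or outpatient status, psychiatric history, and previous treatment where the arms overlap on it.

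State in the same section that A vs B and A vs C compare treatment together with hospital, and that C vs B also reflects prior allopathic treatment. Reconcile sections 2.3 and 2.3.3 on whether Arm C may include patients with no prior allopathic treatment.

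The cost is wording and a few degrees of freedom out of 105 patients, with no new data collection. The set should be fixed before outcomes are seen. It removes bias from the measured covariates, but it cannot separate hospital from treatment.
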